#### **3.3 Research variables:**

- dependent variable(s) (outcomes): HbA1c and time in range (TIR, percentage of time an individual remains with blood glucose levels in a target range of 70 to 180 mg/dL)
- independent variables (causes): non-applicable
- interfering variables (causes): non-applicable
- control variables (causes): non-applicable

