### 4.2 Population and sampling:

All the patients enrolled for KIP will be considered for the cohort, except patients who refuse to share their data or lose follow-up. Patients of both sexes and aged  $\geq 18$  years will be included. We aim to recruit at least 100 participants.

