### 4.3 Inclusion and exclusion criteria:

#### **Inclusion criteria**

1. Diagnosis of T2DM in the electronic medical record of private health insurance companies (HbA1c reading 7% or higher; age  $\geq 18$  years).
2. Willingness to receive phone calls and messages for monitoring the disease and for tele-education.
3. Willingness to use the standard monitoring devices (glucometer), synchronized with the telemonitoring system according to the study protocol throughout the 12-month study period.

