#### 4.9 Statistical analysis

**These activities will be performed by the investigator [name]. [name] and her advisee:**

Analyses will be conducted by comparing pre- and post-intervention parameters of the patients selected for KIP.

For all the measurements, clinical and laboratorial characteristics will be assessed by descriptive statistics. Categorical variables will be expressed as percentages, and continuous variables will be expressed as mean  $\pm$  SD or median (interquartile range). The Kolmogorov-Smirnov test will be used to check data normality. The characteristics of the participants in the different groups (defined according to clinical characteristics) will be evaluated by t-test or Wilcoxon rank test (continuous variables) or Pearson's chi-squared test (categorical variables). Logistic regression will be used to assess the association between independent variables and diabetes mellitus. The analyses will be adjusted for age and sex. Receiver Operational Characteristics (ROC) curves will be performed to evaluate the performance of the suggested models and models that are scientifically sound, and the area under the curve (AUC) will be used to measure the discriminatory power of the identified explanatory variables for T2DM. Statistical analysis will be performed by using RStudio software version 1.3.1093. The significance level will be set at 5%.

Sub-groups (e.g., group I and group II) will be created on the basis of pre-existing conditions described as follows:

Group I: Participants with no or only mild non-proliferative diabetic retinopathy without any macular involvement; chronic kidney disease up to stage 3a (eGFR  $\geq 45$  mL/min/1.73 m^2); participants with no known macrovascular diseases.

Group II: Participants with retinal pathologies documented in the medical records, including proliferative diabetic retinopathy (moderate to severe) or other retinal or macular diseases; or chronic kidney disease stage 3b or 4; or known peripheral vascular, coronary, or cerebrovascular disease.

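### Section 4.9 models diabetes status by logistic regression and ROC/AUC, but a T2DM diagnosis is an entry criterion, so the outcome does not vary in the analysed cohort

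*Protocol*

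**What the plan says.** Protocol section 4.9 first sets out the main comparison: "Analyses will be conducted by comparing pre- and post-intervention parameters of the patients selected for KIP". After descriptive statistics and simple tests it adds a regression: "Logistic regression will be used to assess the association between independent variables and diabetes mellitus". It then plans ROC curves, whose AUC "will be used to measure the discriminatory power of the identified explanatory variables for T2DM". The sentence directly after the logistic one calls for adjustment for age and sex. Diabetes status is thus named as the outcome twice, once for the regression and once for the discrimination analysis.

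Other sections fix who is analysed:

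- Section 4.3, inclusion criterion 1: "Diagnosis of T2DM in the electronic medical record of private health insurance companies (HbA1c reading 7% or higher; age" (the age limit follows).
- Section 4.2: "All the patients enrolled for KIP will be considered for the cohort, except patients who refuse to share their data or lose follow-up". The same section gives the size: "We aim to recruit at least 100 participants".
- Section 4.8, under the disease diagnosis heading, defines T2DM by fasting glucose of at least 126 mg/dL or use of an antidiabetic drug.
- Section 3.3 lists HbA1c and TIR as the dependent variables and has the entry "independent variables (causes): non-applicable".

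**The concern.** A logistic model compares people who have the outcome with people who do not, and an AUC is the probability that a randomly chosen case is ranked above a randomly chosen non-case. Here the entry criterion supplies the cases and nothing supplies the non-cases.

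This is not a detail left open for an analysis plan. The protocol positively states an analysis that its own design cannot support. The analyst would have to drop two named methods or choose another outcome once the data are in hand. An AUC for T2DM published from this cohort would mislead, because readers would take it as discrimination between people with and without diabetes. Logistic regression is also the only named method in section 4.9 that takes covariates, so the adjustment for age and sex has no workable model to attach to.

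**Working it through.** The protocol gives no figure for this component (no event rate, odds ratio or AUC), so there is nothing to reproduce. The check is whether the stated analysis has a solution.

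**Inputs.** Outcome: diabetes yes/no (4.9). Cohort: KIP enrollees with a T2DM diagnosis (4.2, 4.3, 4.9). Size: n = 100, the recruitment minimum (4.2). Covariates: one explanatory variable plus age and sex, giving three slopes. The single explanatory variable is an assumption, as 4.9 lists none.

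**Step 1: cases and non-cases.** Cases = 100, non-cases = 100 − 100 = 0.

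**Step 2: logistic regression.** With every outcome equal to 1, the log-likelihood is −Σ log(1 + exp(−ηᵢ)), where ηᵢ is the linear predictor. With slopes at zero and intercept b it is −100 × log(1 + e^(−b)):

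| Intercept b | Log-likelihood |
|---|---|
| 5 | −0.67 |
| 10 | −0.0045 |
| 20 | −0.0000002 |

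The log-likelihood is bounded above by 0, approaches that bound as b grows and never reaches it. The same holds for any fixed set of slopes, so the data cannot separate one odds ratio from another. A Newton fit to 100 all-case records with simulated covariates stopped with a singular matrix. Software that does print estimates for such data shows only where its iterations stopped, so those values should not be read as a size of effect or of error.

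**Step 3: ROC and AUC.** The AUC averages over case/non-case pairs: 100 × 0 = 0 pairs. Specificity has a denominator of 0. Sensitivity can still be computed, since it needs only cases, but a curve needs both. Recruiting N participants gives N × 0 = 0 pairs, so a larger sample does not help.

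**Step 4: the section 4.8 definition as the outcome.** A non-case would be an enrolled patient with a recorded T2DM diagnosis, no antidiabetic drug and fasting glucose below 126 mg/dL. The protocol does not say how many there would be, so an assumed range of 1% to 10% of 100 is shown. With m non-cases, the null standard error of the AUC is √[(100 + 1) / (12 × m × (100 − m))].

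| Assumed share | Non-cases m | Non-cases per slope (m/3) | Null SE of AUC |
|---|---|---|---|
| 1% | 1 | 0.3 | 0.29 |
| 2% | 2 | 0.7 | 0.21 |
| 5% | 5 | 1.7 | 0.13 |
| 10% | 10 | 3.3 | 0.10 |

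These data would be sparse, and the contrast would be treatment or control status among people with diabetes.

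**Step 5: fit with the objectives.** Sections 2.1 to 2.3 and 3.1 concern HbA1c, TIR, questionnaire measures, hypoglycaemic events and complications. Section 3.2 states that there is no secondary hypothesis. None asks what predicts or discriminates diabetes.

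**The case against.** The strongest objection concerns weight. The main hypothesis is change from baseline in HbA1c and TIR, and section 4.9 opens with that comparison. The faulty model is ancillary, and deleting it would cost the study none of its stated objectives. This stands. A reader might infer that the primary analysis fails too, but the documents do not support that: the pre/post comparison does not use diabetes status as an outcome.

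A second objection is that impossibility is not absolute, because the section 4.8 definition need not hold for every enrollee. This stands in part. One might be tempted to say that the model could never be fitted under any reading, which goes too far. But 4.9 does not link the model to that definition, and a fit obtained that way would not answer the question 4.9 poses.

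Third, section 3.3 sits under the research hypotheses and may describe only the pre/post hypothesis. Its entry on independent variables therefore shows a mismatch of wording with 4.9; it is not separate proof of the error.

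Fourth, one might fault the protocol for having no model of who improves on HbA1c or TIR. No objective asks for one, and such a model could be left to an analysis plan, so its absence is not part of this point.

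It might also be said that glycaemic control was meant where 4.9 says diabetes. Nothing in the text says so, and that reading would require the same rewording.

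**Conclusion.** The point holds for the logistic regression and ROC/AUC component of section 4.9. As written, its outcome is constant by the entry criterion: 100 cases and no non-cases at the minimum sample size, no finite odds-ratio estimates, and an undefined specificity, ROC curve and AUC. This rests on reading diabetes mellitus and T2DM in 4.9 as the condition required for entry, and on there being no comparison group outside KIP; the protocol describes none. Under the section 4.8 definition some fit might be possible, but with few non-cases over the assumed 1% to 10% range and with a different meaning. The stated outcome also differs from the dependent variables in section 3.3 and from every stated objective. The text needs correcting before analysis. The primary comparison of HbA1c and TIR is not affected.

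**What to change.** In section 4.9, do one of the following:

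1. Delete the logistic regression and ROC/AUC analysis of diabetes mellitus. This is the minimal correction, and no stated objective is lost.
2. Keep an adjusted analysis but restate its outcome as one that varies within the cohort and matches the HbA1c/TIR objectives. One option is a linear or mixed model of follow-up HbA1c, adjusted for baseline HbA1c, age and sex.

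If a binary HbA1c outcome is preferred, such as being below the 7% entry threshold at month 12, list a very small predictor set in advance. Assuming that 30 to 40 of 100 participants reach it (the protocol gives no such rate), 10 events per parameter allows 30/10 = 3 to 40/10 = 4 parameters. Age and sex take two, leaving one or two; adding baseline HbA1c leaves none or one. Excluding participants lost to follow-up, as section 4.2 provides, could reduce this further.

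Whichever option is taken, align section 3.3: keep HbA1c and TIR as dependent variables and, if a regression remains, name its independent and control variables in place of the non-applicable entries.

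The cost is a wording change in sections 4.9 and 3.3. HbA1c is already due every three months, and age and sex already serve as adjustment variables, so no new data collection is needed.

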## **5. OUTCOMES**

Expected academic results:

KIP participants should present improved HbA1c and TIR along the intervention as compared to baseline values.

## **6. RISKS AND BENEFITS**

6.1 Risks: The program involves educational actions in health and monitoring (especially glycemic control). Risks are related to disease diagnosis (for example, hypo or hyperglycemia) and measures to mitigate such events. There are also risks involved with data handling (leak, hacker attack, risks to safety and privacy, for instance).

6.2 Paying for participants' expenses regarding the research:  
Not applicable

6.3 Benefits:

Participants will receive information about the primary pathology (diabetes mellitus) and associated factors. Instant alerts will be sent to participant when abnormal glucose levels are detected.

## 7. TIME SCHEDULE

|                                                   | 2022           |   |   |   |   |   |   |   |   |   | 2023 |   |
|---------------------------------------------------|----------------|---|---|---|---|---|---|---|---|---|------|---|
|                                                   | M              | A | M | J | J | A | S | O | N | D | J    | F |
| Specification of objectives and hypotheses.       |                |   |   |   |   |   |   |   |   |   |      |   |
| Survey of the literature.                         |                |   |   |   |   |   |   |   |   |   |      |   |
| Project approval by funding agencies              |                |   |   |   |   |   |   |   |   |   |      |   |
| Project approval by the Research Ethics Committee |                |   |   |   |   |   |   |   |   |   |      |   |
| Operating concepts and variables.                 |                |   |   |   |   |   |   |   |   |   |      |   |
| Data collection.                                  |                |   |   |   |   |   |   |   |   |   |      |   |
| Laboratory tests (if applicable)                  | NON-APPLICABLE |   |   |   |   |   |   |   |   |   |      |   |
| Data compilation.                                 |                |   |   |   |   |   |   |   |   |   |      |   |
| Results analysis.                                 |                |   |   |   |   |   |   |   |   |   |      |   |
| Statistical treatment and data analysis           |                |   |   |   |   |   |   |   |   |   |      |   |
| Discussion and conclusion                         |                |   |   |   |   |   |   |   |   |   |      |   |
| Thesis defense/Presentation                       |                |   |   |   |   |   |   |   |   |   |      |   |
| Publication in scientific journals.               |                |   |   |   |   |   |   |   |   |   |      |   |

Data collection at baseline and the intervention will start on 03/03/2022. Data will be collected again 3, 6, 9, and 12 months after the start of the protocol.

## **8. NECESSARY RESOURCES AND PROJECT COSTS**

8.1 Executing team:

[name]. [name] and [name]

8.2 Equipment and supply:

Not applicable

8.3 Risks associated with the necessary resources:

Not applicable

8.4 Detailed budget:

The funding company will provide R\$100,000.00 (~US\$20,000.00) to fund the project

8.5 Sponsor: KLIVO LICENCIAMENTO LTDA (CNPJ (Corporate Taxpayer Number)15.996.337/0001-85) (See letter attached to the platform)

